**Trial Protocol and Statistical Analysis Plan**

Title: Disclosure of genetic information and change in dietary intake: a randomized

controlled trial

Authors: [name] and [name]

This supplement contains the following items:

1. Summary of trial
2. Original trial protocol, final protocol, summary of changes
3. Original statistical analysis plan, final statistical analysis plan, summary of changes
4. **Summary of trial**

The purpose of this randomized controlled trial is to determine the effect of disclosing diet-related genetic information on dietary intake behaviour. Participants who completed the Toronto Nutrigenomics and Health study will be invited by e-mail to participate in this study. Informed consent will be obtained. Participants who choose to take part will be randomized into an intervention group or a control group (2:1 ratio). All participants will complete a baseline196-item food frequency questionnaire (FFQ) to assess habitual food intake over the past 30 days. Shortly after the baseline assessment, participants in the intervention group will receive a report of personalized dietary recommendations. The report will provide them with information on their gene variants that influence caffeine metabolism, sugar consumption, salt sensitivity and vitamin C metabolism. Participants provided a blood sample for the Toronto Nutrigenomics and these genotypes were determined. The report will explain what the genotypes mean and will provide DNA-based advice for daily intakes of caffeine, sugar, sodium and vitamin C. Participants in the control group will receive Health Canada’s general recommendations for intakes of caffeine, sugar, sodium and vitamin C with no genetic information. Three months after receiving the dietary recommendations, participants in both groups will complete a second FFQ to examine potential short term changes in dietary intake. A third FFQ will be collected one year after baseline, to examine potential long term changes. The nutrient analysis between the three FFQs will be compared to identify changes in dietary intake of caffeine, sugar, sodium and vitamin C. The intervention group FFQs will be compared to the control group FFQs to examine how changes differed when dietary advice was personalized based on genotype.

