**References:**

1. Sterling R (2008) The online promotion and sale of nutrigenomic services. Genet Med. 10:784-796.

1. **Original trial protocol**

- 200 subjects (aged 20-35 years) will be recruited from the Toronto Nutrigenomics and

Health Study.

- Exclusion criteria:

o <100 mg of caffeine/day

o <10% energy from total sugars/day

o <1500 mg of sodium/day

o Vitamin C supplement use

o Pregnant/nursing

- Subject characteristics (age, sex, ethnicity, level of education) will be collected using a

questionnaire.

- A food frequency questionnaire (FFQ) will be collected at 0, 3 and 12 months.
- Subjects will be randomized to an intervention group or control group (2:1 ratio) and

dietary advice reports will be given.

- Control group: general dietary recommendations for caffeine, vitamin C, added

sugars and sodium.

- Intervention group: DNA-based dietary recommendations for caffeine, vitamin C,

added sugars and sodium.

- Copy of dietary advice reports given at monthly intervals.

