**Final protocol:**

Same as original protocol except 157 subjects were recruited.

S**ummary of changes:**

No changes were made to the original study protocol. 157 subjects were recruited instead of the

original goal of 200. Routine updates were made to the protocol’s trial record on

http://clinicaltrials.gov (NCT01353014) to reflect study progress (e.g. enrolment status,

anticipated follow-up and completion dates, actual follow-up and completion dates).

1. **Original statistical analysis plan**

- Subject characteristics between the intervention and control group will be compared using

a Student’s t-test for continuous variables (age) and a Chi-square test for categorical

variables (sex, ethnicity, level of education).

- General linear model will be used to identify changes in the mean intakes of caffeine,

added sugars, vitamin C and sodium from baseline to 3 months and baseline to 12 months.

- Tukey’s test for multiple comparisons will be applied to determine whether changes in

intake of the intervention risk and intervention non-risk groups differ from the change in

intake of the control group.

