**Final statistical analysis plan (changes from original plan are indicated in bold):**

- Subject characteristics between the intervention and control group will be compared using

a Student’s t-test for continuous variables (age) and a Chi-square test for categorical

variables (sex, ethnicity, level of education).

- General linear model used to identify changes in the mean intakes of caffeine, added

sugars, vitamin C and sodium from baseline to 3-months and baseline to 12-months.

- Tukey’s test for multiple comparisons applied to determine whether changes in intake of

the intervention risk and intervention non-risk groups differed from the change in intake of

the control group.

- **General linear model used to compare baseline intakes of caffeine, vitamin C, added**

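### Each genotype subgroup of the intervention arm is compared with one undivided control group, so the only written treatment contrasts are not protected by randomisation; the size of any bias is unknown

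*Supplement*

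**What the plan says.** Allocation is by participant. Under Original trial protocol: "Subjects will be randomized to an intervention group or control group (2:1 ratio"). The Final protocol keeps this: "Same as original protocol except 157 subjects were recruited". No stratification by genotype is described.

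The Final statistical analysis plan gives one between-group test of change, by Tukey's method. It asks whether "the intervention risk and intervention non-risk groups differed from the change in intake of" a single, undivided set of controls. Control participants receive "general recommendations for intakes of caffeine, sugar, sodium and vitamin C with no genetic information", and nothing divides them by genotype. The plan has no genotype covariate and no arm-by-genotype interaction. The only adjustment is for ethnicity, and it applies where baseline intake differed significantly between ethnic groups.

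Three statements in the Summary of trial bear on this:
- The report covers "gene variants that influence caffeine metabolism, sugar consumption, salt sensitivity and vitamin C metabolism".
- On availability of genotypes: "Participants provided a blood sample for the Toronto Nutrigenomics and these genotypes were determined". All participants come from that parent study.
- On the comparison of arms: "The intervention group FFQs will be compared to the control group FFQs". The analysis plan does not turn this into a stated test.

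**The concern.** Randomisation makes the two whole arms comparable, and it makes risk carriers in one arm comparable with risk carriers in the other. It does not make risk carriers in one arm comparable with everyone in the other. As written, each contrast combines the effect of disclosure with any difference between genotypes in how intake would have changed anyway.

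The two errors have opposite signs. A genotype difference in change could therefore look like a genotype-specific response to disclosure even if disclosure did nothing. The same structure applies to all four nutrients and both follow-up times, and a larger sample would not cure it.

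**Working it through.** The plan states no significance level, effect size, SD or genotype frequency, so there is no figure of its own to reproduce.

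**Inputs**
- From the documents: 157 participants at 2:1. 157 × 2/3 = 104.7 and 157 / 3 = 52.3, taken as 105 and 52.
- Assumed: two-sided 5% level; complete follow-up; unit SD of change in every group; the same p in both arms; p = 0.3, 0.5 or 0.7; d from 0 to 0.5 SD.
- Tukey critical value for three groups and 154 degrees of freedom: 3.347 / √2 = 2.367.

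**Bias.** Let mean change without disclosure be m in non-risk and m + d in risk participants, with disclosure effects eR (risk) and eN (non-risk).
- Control mean: m + p·d.
- Risk contrast: (m + d + eR) − (m + p·d) = eR + (1−p)d.
- Non-risk contrast: (m + eN) − (m + p·d) = eN − p·d.
- Genotype-weighted average of the two biases: p(1−p)d − (1−p)p·d = 0. The whole-arm comparison is therefore unbiased.

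**False-positive rate of the risk contrast when eR = 0.** The planned SE is √(1/(105p) + 1/52). With shift s = (1−p)d / SE, the rate is Φ(s − 2.367) + Φ(−s − 2.367). At p = 0.5, with 52 in the risk group, SE = √(1/52 + 1/52) = 0.196.

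| p | d (SD) | Bias (SD) | SE | s | Rate |
|---|---|---|---|---|---|
| 0.5 | 0 | 0 | 0.196 | 0 | 1.8% |
| 0.5 | 0.1 | 0.05 | 0.196 | 0.26 | 2.2% |
| 0.5 | 0.2 | 0.10 | 0.196 | 0.51 | 3.4% |
| 0.5 | 0.3 | 0.15 | 0.196 | 0.77 | 5.5% |
| 0.5 | 0.5 | 0.25 | 0.196 | 1.28 | 14% |
| 0.3 | 0.5 | 0.35 | 0.226 | 1.55 | 21% |
| 0.7 | 0.5 | 0.15 | 0.181 | 0.83 | 6% |

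The non-risk contrast mirrors this with p and 1−p exchanged.

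**Genotype-matched contrasts.** The bias is zero for any d. A simulation of 20,000 runs per setting, with d from 0 to 0.75 SD and each of the two contrasts tested at 0.025, gave a chance of any false positive between 4.5% and 5.1%.

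**Precision of the matched risk contrast.** SE = √(1/(105p) + 1/(52p)).
- p = 0.7: 0.181 to 0.203, up 12%.
- p = 0.5: 0.196 to 0.240, up 22%.
- p = 0.3: 0.226 to 0.310, up 37%.

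**Interaction.** SE = √(1/(105p) + 1/(105(1−p)) + 1/(52p) + 1/(52(1−p))). This is 0.34 SD at p = 0.5 and 0.37 SD at p = 0.3 or 0.7. Multiplying by 1.96 + 0.84 = 2.80, the interaction detectable with 80% power at two-sided 5% is about 0.95 to 1.04 SD.

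**The case against.** The best defence is that the outcome is change from baseline, so stable genotype differences in intake cancel. Of the four variants, the Summary of trial ties only one directly to intake (sugar consumption). The others concern metabolism or sensitivity. That stands, and it means d may be small or zero. It does not cover differing room to change, regression to the mean, or a different response to general advice.

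A second defence is the ethnicity adjustment. The Summary of changes reports a significant baseline difference between two ethnic groups and says ethnicity was added as a covariate. It would be wrong to treat an ancestry effect as wholly uncontrolled. The adjustment is conditional, however, and does not stand in for genotype within an ethnic group.

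A third is that the whole-arm comparison is sound. That is correct, but the final plan does not write it out as a test.

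A reader might go further and infer that the planned contrasts are materially biased. The documents do not support this, because they contain no evidence on d. A reader might also infer that opposite changes in the two genotype groups are what the trial hopes to find. The Summary of trial states a neutral aim, and no directional hypothesis appears.

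**Conclusion.** The structural fault holds: the only treatment contrasts in the final plan set a genotype-defined part of one arm against the whole of the other, and nothing in the plan separates genotype from disclosure. Its size cannot be determined. It is nil if genotype is unrelated to change under general advice, slight at d = 0.1 to 0.2 SD, and serious at d = 0.5 SD unless the subgroup in question makes up most of the sample.

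Two inferences support this. The control group is taken to be of mixed genotype because no selection by genotype is described. Control genotypes are taken to be on file because all participants come from the genotyped parent study.

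**What to change.** Revise the final analysis plan as follows.
1. Classify control participants by the genotypes determined in the parent study, separately for each nutrient's variant.
2. For each nutrient, fit a model with arm, genotype and their interaction in all randomised participants.
3. Report intervention risk against control risk and intervention non-risk against control non-risk, with a stated adjustment across the two contrasts (for example Bonferroni, 0.025 each) in place of the three-group Tukey test.
4. Report the interaction estimate with its interval.
5. Write out the whole-arm comparison of intervention with control as the randomised test.

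This needs a recoded factor and new wording, but no new data if the control genotypes are on file. The price is the wider intervals shown above. In particular, a non-significant interaction in a trial of this size should not be read as evidence that the response is the same in both genotypes.

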**sugars and sodium between ethnic groups (Caucasian, East Asian and South Asian).**

- **Ethnicity was adjusted for in dietary intake analyses if a significant difference was**

**observed at baseline between ethnic groups.**

**Summary of changes:**

- General linear model used to compare baseline intakes of caffeine, vitamin C, added sugars

and sodium between ethnic groups (Caucasian, East Asian and South Asian). Ethnicity was

adjusted for in dietary intake analyses if a significant difference was observed at baseline

between ethnic groups.

- - **Rationale:** A significant difference in baseline nutrient intake was observed

between two ethnic groups. Therefore, we modified our statistical analysis plan to

include ethnicity as a covariate in the general linear model used to identify

changes in nutrient intakes.
